#### Mood and quality of life outcomes

The primary outcome of depressed mood will be assessed using the PHQ-9 [53], a well-established self-report measure of depression in medical populations. A PHQ-9 score ≥ 10 is a well-established cut off indicating likely clinical depression. Secondary mood and quality of life outcomes will include the 10-item Center for Epidemiologic Studies Depression Scale [66] (CESD-10). The CESD-10 is included as a secondary outcome because it has a timeline of only 1 week and thus can give a better measurement of post-discharge, pre-randomization depressed mood (i.e., mood in the time period between Session 1 and randomization)**.** We will measure positive and negative affect using the 10-item Positive Affect Negative Affect Scales [67] (PANAS). Low levels of positive affect represent one aspect of anhedonia (i.e., low levels of positive emotions). We will also measure reactive anhedonia (i.e., blunted response to the occurrence of pleasurable events) using the Snaith Hamilton Pleasure Scale [68, 69] (SHAPS). Stress will be assessed using the Perceived Stress Scale [70] (PSS-4). Health Related Quality of Life will be measured using the 12-Item Short Form Health Survey [71] (SF-12).

#### Cardiac health outcomes

Exercise capacity will be assessed using the self-report Duke Activity Status Index [72] (DASI). Major Adverse Cardiac Events [73–75] (MACE; i.e., hospitalization for unstable angina, urgent coronary revascularization, and myocardial infarction according to standard American Heart Association criteria) and all-cause mortality will be tracked for up to 3 years (36 months post-discharge)*.* We will obtain records from any hospitalization or outpatient revascularization reported during assessments or follow-up phone calls. For any participant lost to follow-up, we will review medical records at recruitment hospital sites and mortality databases, as well as contact participant provided emergency contacts to obtain MACE/mortality status. Independent coding of MACE events will be completed by two study cardiologists using a structured coding form. They will meet to resolve any coding disagreements and a third cardiologist will resolve any disagreements on which a consensus cannot be reached. See Table 2 for details of changes to cardiac health outcome measures due to COVID-19.

Adverse events and patient safety will be tracked throughout the study, including hospitalizations, CO readings indicating toxic environmental exposure, unexpected side effects to the nicotine patch, and suicidality. All staff will be trained in a safety protocol which includes responses to both physical (e.g., CO readings indicating high environmental exposure) and psychological safety events (suicidality). A safety committee consisting of site PIs and an independent investigator otherwise not associated with the study will meet yearly to discuss all adverse events and other safety issues. A DSMB was not required by the funder at the time of study initiation.

#### Hypothesized BA mediators

Engagement in pleasant and valued activities will be measured using the 9-item Behavioral Activation for Depression Scale [76] (BADS) and the frequency items on the 20-item Pleasant Events Schedule [77, 78] (PES).

#### Treatment acceptability

Will be assessed quantitatively using the Client Satisfaction Questionnaire [79] (CSQ-8).

#### Potential confounders

We will collect data at all follow-ups on potential confounders of treatment effects so we can control for these variables as needed in analyses (i.e., data on dose of treatment received, cardiac rehabilitation attendance, depression or smoking counseling or medication use outside of the study, engagement in exercise, diet, and adherence to medications).

#### Blinding

Only the study statistician and data manager will have access to the allocation to treatment order prior to randomization. Outcomes assessors will be blind to treatment condition throughout the study. They will conduct end-of-treatment (12 week) and 6-, 9-, and 12-month assessments, and bi-annual calls monitoring for MACE/mortality. If the assessor learns a participant’s randomization assignment through any means (i.e., becomes unblinded), another assessor will take over that participant’s remaining assessments/calls. The study cardiologists will be blind to treatment condition throughout the study and will code records for the occurrence and type of MACE.

#### Retention and incentives for participation

Based on our pilot work and previous clinical trials in which we have obtained follow up completion rates of 85–90% (e.g., R01AT006948; K23HL107391; R44DA022167) [80, 81], we expect to complete follow-up assessments with at least 80–85% of participants. A comprehensive maintenance program similar to our previous studies will be used to ensure this level of retention.

Participants will receive $50 at each primary assessment completed [Baseline 1, Baseline 2, End-of-Treatment (12 weeks), and 6-, 9-, and 12-month follow-ups]. Transportation costs (taxi service, bus fare, mileage, and/or parking vouchers) to an in-person assessment will be paid for by the study. Participants will be paid $5 each for completion of counseling sessions 3, 4, 5, and 6 and a $20 bonus if that participant completes all four of these sessions. Remuneration for counseling sessions 3–6 was added (see Table 2) during the trial based on participant feedback that phone calls were using up limited cell phone minutes. For each brief phone assessment completed from 18 to 36 months post-discharge, participants will be compensated $10.

We will provide participants with study marketing materials (e.g., coffee mugs, water bottles, tote bags) that will include the study name, logo, phone number, and email. We will offer one item at Baseline 2 (1 week post-discharge) and one item at any follow-up assessment visit (12w, 6 m, 9 m, 12 m) attended in person. New Years and mid-Summer cards with the study logo will be sent to all study participants through the duration of their participation. Incentives and provision of marketing materials will be identical in each condition. We will send text, email, and/or mail reminders in advance of each assessment. We will obtain three “emergency contacts” (i.e., who will know how to reach the participant should their phone number be out of service) from each participant and these contacts will be updated as needed throughout the study.

Participants who do not have regular access to a phone or those who lose access to a phone during the first year of enrollment will be offered a study issued cellphone to complete study activities. Upon completion of the 12-month outcomes assessment, participants using study issued cellphones will be compensated $20 for returning the phone to study staff.

#### Interventionist background and training

Counseling will be completed by individuals with a Bachelor’s or Master’s degree in health education or a related field. All counselors will complete tobacco treatment specialist training, read materials on tobacco treatment [55], BA [54], and ACS [82–84], listen to mock sessions completed by clinical psychologists, and complete mock sessions with other study staffs. Use of tobacco treatment specialists greatly improves cost effectiveness, real world applicability, and potential for future dissemination.

#### Intervention fidelity

We will implement intervention fidelity procedures developed by the NIH Behavioral Change Consortium [85]. We will use detailed written manuals for each intervention condition to minimize any potential for contamination between conditions. Counselors will be trained in each manual by two clinical psychologists.

Counselors will audio record all sessions in both conditions and complete a self-report treatment fidelity checklist following each session in both conditions. Supervisors will review audio recordings of all sessions of each counselor’s first patient in each condition and a random 10% of all subsequent sessions in both conditions. Supervisors will complete the treatment fidelity checklist for each session they review. Counselors will have weekly supervision with clinical psychologists during which any barriers to fidelity or drift from the manual will be addressed.

#### Data management

Data will be managed by a PhD biostatistician and a data manager. All staff on the study will be trained in proper data management and security. Paper files will be stored in a locked cabinet within a locked room. All digital data will be stored on either secure, password protected institutional servers or in REDCap. Participant tracking will be conducted using custom software on a SQL server. Randomization will be completed in REDCap. REDCap will also be used to record informed consent and HIPAA authorization when completed electronically.

#### Power

The proposed study is fully powered for both Aim I primary outcomes (i.e., biochemically confirmed 7-day point prevalence abstinence and depression symptoms on the PHQ-9 over 12 months post discharge). Based on existing data at the time of study design [36, 38, 86], we expect 7-day point prevalence rates to differ by 8% (29% in control, 37% in BAT-CS) at 12 months, representing an odds ratio of 1.4 at 12 months. We will analyze our data longitudinally (see below), thus we base our sample size on the longitudinal effect across the 4 follow-ups (i.e., end-of-treatment and, 6, 9, and 12 months post discharge). We expect a *longitudinal* odds ratio of 1.33 ending with an 8% between-group difference at 12 months as described above. It is important to note that experts have proposed that increasing rates of smoking cessation in ACS patients by even 5% would have a large impact on public health [87]. Given the assumptions above and an alpha level of 0.05, a total sample size of 324 participants would be required in order to have sufficient (80%) power to test the *longitudinal* effect on intent-to-treat 7-day point prevalence abstinence over 1 year post-discharge. This sample will be more than sufficient (power > 80%) to detect even small longitudinal effects on depression symptoms over 1 year (i.e., with 324 participants we have 80% power to detect between group effect of f squared = 0.03).

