**Method/design:**

The overall aim of the current study is to conduct a fully powered efficacy trial enrolling 324 smokers with ACS and randomizing them to 12 weeks of an integrated smoking cessation and mood management treatment [Behavioral Activation Treatment for Cardiac Smokers (BAT-CS)] or control (smoking cessation and general health education). Both groups will be offered 8 weeks of the nicotine patch if medically cleared. Counseling in both arms will be provided by tobacco treatment specialists. Follow-up assessments will be conducted at end-of-treatment (12-weeks) and 6, 9, and 12 months after hospital discharge. We will track major adverse cardiac events and all-cause mortality for 36 months post-discharge. Primary outcomes are depressed mood and biochemically validated 7-day point prevalence abstinence from smoking over 12 months.

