### Aim I

Test the efficacy of BAT-CS versus control on depressed mood and smoking cessation. *Hypothesis 1a*: Patients treated with BAT-CS will demonstrate significantly greater improvements in mood and significantly higher rates of biochemically verified 7-day point prevalence abstinence over 12 months than control patients. This trial is powered for hypothesis 1a analyses. *Hypothesis 1b*: Patients treated with BAT-CS will also have higher rates of 30-day point prevalence and continuous abstinence since discharge and longer time to smoking lapse and relapse than control patients.

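### The stated 80% power for abstinence does not follow from an odds ratio of 1.33 and 324 participants: two-sided power is at most about 67–73%, and less with any positive within-person correlation

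*Protocol article*

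**What the plan says.** The Power section expects 12-month abstinence rates to "differ by 8% (29% in control, 37% in BAT-CS) at 12 months, representing an odds ratio of 1.4 at 12 months". It then says the sample size rests on the effect across the four follow-ups (end of treatment, 6, 9 and 12 months), with a longitudinal "odds ratio of 1.33 ending with an 8% between-group difference at 12 months as described above". The claim, made at the 5% significance level, is that "a total sample size of 324 participants would be required in order to have sufficient (80%) power" for the longitudinal effect on intent-to-treat 7-day point prevalence abstinence.

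The test is described under Primary outcome analyses. It is a GEE with a logit link that regresses smoking status on intervention group, with an unstructured working correlation to allow for dependence within a person.

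The claim is repeated elsewhere. The Abstract says the aim is to "conduct a fully powered efficacy trial enrolling 324 smokers", the Background describes the trial in the same terms, and Aim I says "This trial is powered for hypothesis 1a analyses".

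**The concern.** Four correlated binary results on one person cannot carry more information about an average group effect than four independent results, as long as the correlation is not negative. That gives a ceiling on power that needs no assumption about the size of the correlation. If the ceiling is below 80%, the stated combination of odds ratio, sample size and power is wrong as written.

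Abstinence is one of two primary outcomes, and readers will judge a non-significant result by the advertised power. If the true power at the assumed effect is well below 80%, such a result says much less against that effect than the article implies.

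**Working it through.** **Inputs from the article:** total 324; alpha 0.05; longitudinal odds ratio (OR) 1.33; four follow-ups; 29% and 37% abstinent at 12 months; GEE with a group effect.

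**Assumptions, because the article gives no value:** 1:1 allocation (162 per arm); two-sided test unless noted; within-person correlation ρ, exchangeable, from 0 to 0.7; control abstinence before 12 months, varied from 29% to 50%. No missing data are applied, although the article expects 80–85% completion. That choice favours the plan.

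**Formulas**
- BAT-CS rate p2 from control rate p1: odds2 = OR × p1/(1 − p1).
- Single-visit variance of the log OR: V = 1/[162·p1(1 − p1)] + 1/[162·p2(1 − p2)].
- Average effect over four visits: SE = √[V(1 + 3ρ)/4].
- Power = Φ(ln OR/SE − 1.960) two-sided, or Φ(ln OR/SE − 1.645) one-sided.

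**Step 1: trying to reproduce 80% at 324**
- OR 1.4 at every visit, control 29%, ρ = 0: p2 = 0.364, V = 0.0567, SE = 0.1190, ln 1.4 = 0.3365, ratio 2.827, two-sided power 80.7%. This is close to the stated figure, but the Power section says the longitudinal OR is 1.33.
- OR 1.33, one-sided 0.05, ρ = 0: 77% (control 29%), 80% (control 35%), 82% (control 46%).

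**Step 2: the inputs as stated, two-sided, ρ = 0**
- Control 29%: p2 = 0.352. V = 0.02998 + 0.02706 = 0.05704. SE = √(0.05704/4) = 0.1194. ln 1.33 = 0.2852. Ratio 2.388. Power = Φ(0.428) = 67%.
- Control 46%, about where the binomial information is greatest: p2 = 0.531, V = 0.0496, SE = 0.1114, ratio 2.560. Power = Φ(0.600) = 73%.

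So 73% is the two-sided ceiling over all control rates and all ρ ≥ 0.

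**Step 3: effect of positive correlation (OR 1.33, N = 324)**

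| ρ | Two-sided, control 29% to 46% | One-sided, control 29% to 46% | OR detectable at 80% power, two-sided |
|---|---|---|---|
| 0 | 67–73% | 77–82% | 1.37–1.40 |
| 0.1 | 55–61% | 67–73% | 1.43–1.46 |
| 0.3 | 41–46% | 54–58% | 1.54–1.58 |
| 0.5 | 33–37% | 45–49% | 1.64–1.69 |
| 0.7 | 27–31% | 39–42% | 1.74–1.79 |

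With correlation that decays between visits (AR(1), parameter 0.5–0.7), two-sided power is 31–44%.

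**Step 4: cross-check at 12 months alone.** The OR for 37% against 29% is (0.37/0.63)/(0.29/0.71) = 1.44, given in the article as 1.4. With 162 per arm, that single comparison has about 33% power.

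**The case against.** **Sidedness is not stated, and hypothesis 1a is directional.** This is fair. A one-sided 0.05 test with independent results reaches 77–82%, so a reader who infers that 80% is unreachable under any reading goes too far. The rescue is fragile, though: one-sided power is already 67–73% at a correlation of 0.1, and the analysis section itself plans for within-person correlation.

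**The calculation may have used OR 1.4.** Possibly. With independent results, OR 1.4 gives 80.7%, and combining OR 1.4 with a one-sided test needs about 325 participants at correlation 0.1. But the text ties 324 to 1.33, and OR 1.4 at correlation 0.3 gives only about 54% two-sided.

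**The longitudinal effect may be a group-by-time slope.** A reader might infer that this reading has still less power. Not so if 1.33 is the change per visit: the slope variance is then V(1 − ρ)/5, and power is 0.76, 0.89, 0.97 and 0.998 at ρ = 0, 0.3, 0.5 and 0.7. However, the OR would have to grow by 1.33³ = 2.35 between week 12 and month 12. To end at 1.4 it would have to start near 1.4/2.35 = 0.6, favouring control. The described model also has a group effect, not a slope.

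**A condensed article may leave the correlation and visit-specific rates to the full protocol or SAP.** Agreed; their absence is not the finding. No non-negative correlation supplied elsewhere brings the stated two-sided figure to 80%.

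**Conclusion.** The point holds. For a two-sided 0.05 test of the average group effect at OR 1.33 with 324 participants, power is at most about 67% (control abstinence 29%) to 73% (control about 46%), not 80%. This rests on 1:1 allocation, non-negative correlation and complete data.

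The size of the shortfall below that ceiling depends on a correlation the article does not give: about 41–46% at 0.3, 33–37% at 0.5 and 27–31% at 0.7. A reader might infer that the trial has an established one-in-three chance of detecting the assumed effect. The documents do not support that as a fact; it is conditional on a correlation around 0.5.

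A reader might also infer that the article claims joint power for mood and abstinence together and fails there too. The Power section claims power for each primary outcome, so there is no joint figure to contradict. This point concerns abstinence only.

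**What to change.** Enrolment need not change. In the Power section, replace the statement of 80% power at OR 1.33 with one of two things:
- the power that 324 participants give, with the correlation, sidedness and control rates it assumes; or
- the OR detectable at 80% power with 324, which is about 1.5–1.8 at correlation 0.3–0.7, two-sided.

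If 324 came from OR 1.4, a one-sided test or independent results, say so and make the text agree. Drop the description fully powered for abstinence in the Abstract, Background and Power sections, and qualify the sentence in Aim I. Carry the restated figure into the results paper.

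The cost is a few sentences and a less favourable headline figure. No estimate, test or trial procedure changes.

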#### Primary outcome analyses

We will estimate the effect of the interventions on smoking cessation (biochemically verified 7-day point prevalence abstinence) at end-of-treatment and follow-ups (6, 9 and 12 months) using a longitudinal regression model implemented with generalized estimating equations (GEE) with robust standard errors [91, 92]. Specifically, we will regress smoking status on intervention group (BAT-CS vs. control) and potential covariates (cardiac rehabilitation attendance, cessation treatment outside of the study, other baseline variables will be included as covariates if they are both not balanced by randomization and are correlated with the outcome under consideration at *p* < 0.10 level) using binomial errors, a logit link function, and a working unstructured correlation to accommodate within-subject correlation.

We will use a series of longitudinal mixed effects regression models to estimate the effect of BAT-CS versus control on depressed mood (PHQ-9) at end-of-treatment and subsequent follow-ups, controlling for baseline depression, cardiac rehabilitation attendance, depression treatment outside of the study, and any other variables not balanced by randomization that are correlated with depressed mood at follow-ups at a modest *p* < 0.10 level. Models will include a subject-specific intercept to adjust for repeated measurements within participant over time. Modeling is done using a likelihood-based approach and thus makes use of all available data (on the intent to treat sample) without directly imputing missing outcomes, to produce consistent estimates of the regression parameters.

For primary outcomes (i.e., biochemically verified 7-day point prevalence abstinence and PHQ-9) we will conduct a per-protocol analysis (with parallel models to those described above) to assess differences between groups among those who completed a substantial number of treatment sessions. Per protocol will be defined completing at least four treatment sessions in both treatment groups.

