**Fig. 2 Fig2:**
[figure not shown]
Design overview

**Table 1 Tab1:** Assessments by time point

	Screen	Baseline 1	Baseline 2	Each session	12 weeks/end-of-treatment	6, 9, 12 months	18, 24, 30, and 36 months
*Screening fully*							
Medical diagnosis, current smoking, and other inclusion/exclusion criteria	X						
Cognitive functioning (MMSE [43])	X						
*Participant characteristics*							
Demographics (age, race, etc.)		X					
Medical and smoking history		X					
Nicotine dependence (FTND [50])		X					
Motivation to quit (contemplation ladder [51])		X	X				
MN withdrawal scale [52]			X				
*Primary outcomes*							
Current smoking/smoking since last contact		X	X	X	X	X	X
Use of other tobacco products		X	X	X	X	X	X
Saliva sample for cotinine testing			X		X	X	
Exhaled breath sample for CO testing			X		X	X	
Depressive symptoms (PHQ-9 [53])		X	X		X	X	X
Depressive symptoms (CESD-10 [66])		X	X		X	X	
*Secondary outcomes*							
Positive and negative affect (PANAS [57])		X	X		X	X	X
Reactive anhedonia (SHAPS [68, 69])		X	X		X	X	
Perceived stress scale (PSS-4 [70])		X			X	X	
Health related quality of life (SF-12 [71])		X			X	X	
Exercise tolerance (DASI [72])		X			X	X	
MACE/mortality					X	X	X
Adverse event monitoring			X	X	X	X	X
*Hypothesized BA mediators*							
Pleasant/valued activities (BADS [76], PES [79, 80])		X			X	X	
*Acceptability*							
Treatment acceptability (CSQ-8 [81])					X		
*Potential confounders*							
Medication adherence questions [88, 89]		X			X	X	
Diet/exercise questions [92]		X			X	X	
Counseling sessions attended				X			
Cardiac rehabilitation attendance					X	X	
Outside of study depression treatment					X	X	
Outside of study smoking cessation treatment					X	X	

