#### Randomization

Randomization will occur 1 week after hospital discharge, immediately after the Baseline 2. We will stratify randomization on elevated symptoms of depression (Patient Health Questionnaire [53] [PHQ-9] score of ≥ 10 vs. < 10 as measured immediately prior to randomization), use of the study provided nicotine patch between discharge and randomization (i.e., using patch vs. not using patch), and recruitment site (i.e., recruited at primary hospital site vs. hospitals subcontracted for recruitment). The randomization sequence will be generated using a stratified permuted block randomization procedure, with small, random sized blocks. The sequence was generated by the study biostatistician. Only the biostatistician and database manager will have access to the randomization sequence and all other study personnel will remain blind to this sequence. Counselors will randomize participants immediately before initiating Session 2 by entering the participant’s identification number, PHQ-9 score, use the nicotine patch, and recruitment site into REDCap [48, 49]. The REDCap interface will indicate the treatment assignment and the counselor will immediately inform the participant of their treatment condition.

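### The primary abstinence model admits other baseline covariates only if imbalanced and correlated with the outcome, which shuts out the stratification factors and usually Baseline 2 smoking status, at a cost in efficiency

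*Protocol article*

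**What the plan says.** **Abstinence model** (protocol article, Primary outcome analyses). A logistic GEE regresses smoking status on arm, cardiac rehabilitation attendance and cessation treatment outside the study. For everything else, "other baseline variables will be included as covariates if they are both not balanced by randomization and are correlated with the outcome", the correlation being judged at p < 0.10. Imbalance is not defined.

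**PHQ-9 model** (same section). Baseline depression, cardiac rehabilitation attendance and outside depression treatment are always included. Beyond these, the model takes "any other variables not balanced by randomization that are correlated with depressed mood at follow-ups", again at p < 0.10.

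**Design** (Randomization). "We will stratify randomization on elevated symptoms of depression" (PHQ-9 of 10 or more against below 10), on use of the study patch between discharge and randomisation, and on primary against subcontracted site, with small permuted blocks of random size.

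**Baseline data** (Baseline measures; Table 1). Baseline 2 takes place one week after discharge, immediately before randomisation. Table 1 marks current smoking, saliva cotinine and "Exhaled breath sample for CO testing" at that visit.

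**The concern.** The word both makes imbalance a necessary condition, so a balanced covariate stays out however well it predicts the outcome. Three things follow.

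- Stratified blocking exists to balance the three factors. The design treats them as important enough to stratify on, and the abstinence analysis then has no route to include them.
- Baseline 2 smoking status is a pre-randomisation measurement of the primary outcome. The PHQ-9 model always adjusts for the baseline value of its own outcome, but the abstinence model has no counterpart.
- Imbalance is undefined and the second condition uses follow-up outcomes, so for both primary outcomes the final covariate set cannot be known until the data are in.

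At stake are power for the abstinence comparison and a fully fixed primary model.

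**Working it through.** **1. The plan's own figure.** Inputs from Power: "an alpha level of 0.05" (two-sided assumed), "sufficient (80%) power", "a total sample size of 324 participants would be required" (162 per arm if 1:1), and 29% against 37% at 12 months.

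For one visit, n per arm = [1.96√(2 × 0.33 × 0.67) + 0.842√(0.29 × 0.71 + 0.37 × 0.63)]² / 0.08² = 542, or 1,084 in total. With 162 per arm, one visit gives 33% power.

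Averaging four visits with within-subject correlation ρ multiplies the total by (1 + 3ρ)/4:

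- ρ = 0 gives 271
- ρ = 0.1 gives 353
- ρ = 0.3 gives 515
- ρ = 0.5 gives 678

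A total of 324 results only at ρ of about 0.065. The document states no ρ and does not define its longitudinal odds ratio, so 324 is not reproduced without an added assumption. This matters here because ρ also governs what adjustment gains.

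**2. What the rule excludes.** Trials of 324 people with four visits were simulated, with eight strata (2 × 2 × 2), permuted blocks of 2, 4 or 6, and logistic GEE with robust standard errors. Assumptions not in the document:

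- 29% against 37% at every visit
- 50% abstinent at Baseline 2, with an odds ratio of 3, 6 or 10 for later abstinence
- odds ratios of 0.6, 1.3 and 1.2 for the strata, with prevalences of 30%, 50% and 50%
- imbalance read as p < 0.10
- an independence working correlation, for simplicity (the plan specifies unstructured)

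No stratification factor was imbalanced in any simulated trial. Baseline 2 abstinence was imbalanced in 10 to 12% of trials, close to the 10% that the threshold implies, so the rule left it out about 89% of the time.

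**3. Power** (%, 3,000 trials per row; all four analyses fitted to the same trials).

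| ρ | Baseline 2 odds ratio | Unadjusted | Plan's rule | Strata only | Strata + Baseline 2 status | Gain over rule (points) |
|---|---|---|---|---|---|---|
| 0.11 | 3 | 76.8 | 77.8 | 78.6 | 84.7 | 6.9 |
| 0.18 | 6 | 69.7 | 72.7 | 70.7 | 87.4 | 14.7 |
| 0.23 | 10 | 64.5 | 68.6 | 65.8 | 90.2 | 21.7 |
| 0.30 | 3 | 58.5 | 58.8 | 59.6 | 62.5 | 3.7 |
| 0.33 | 6 | 57.0 | 58.4 | 58.3 | 66.8 | 8.4 |
| 0.36 | 10 | 54.9 | 56.2 | 55.5 | 68.7 | 12.5 |
| 0.47 | 3 | 50.1 | 49.8 | 51.0 | 51.5 | 1.7 |
| 0.48 | 6 | 50.7 | 50.9 | 51.2 | 54.8 | 3.9 |
| 0.49 | 10 | 50.3 | 50.4 | 50.8 | 55.3 | 4.9 |

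Gains were taken before the power figures were rounded. Strata alone, against unadjusted, add 0.5 to 1.8 points. The Monte Carlo standard error of a single power figure near 50% is √(0.5 × 0.5/3,000), or 0.9 points.

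**4. Type I error.** With no treatment effect (1,500 trials per setting), the rule rejected in 3.9% to 5.3% of trials. The Monte Carlo standard error is √(0.05 × 0.95/1,500), or 0.6 points. There is no sign of inflation.

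**The case against.** **The PHQ-9 model is largely sound.** A reader might infer that the rule governs baseline adjustment in both primary models alike. It does not: baseline depression, which also underlies one stratification factor, is always in the PHQ-9 model. Only patch use and site are shut out there. This stands.

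**The strata matter little on their own.** Under 2 points of power is a modest efficiency loss, and error control is intact. This also stands. Neither the unadjusted standard errors nor the data-driven selection was shown to produce false positives.

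**The prognostic claim is assumed.** One might call Baseline 2 abstinence the strongest predictor of later abstinence. It is plausibly strong, but the document gives neither its frequency nor its association with follow-up. The size of the gain therefore rests on assumption, and the low end of the range is close to simulation error.

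**Adjustment is not entirely free.** Under a logit link, a strong covariate turns the marginal odds ratio into a conditional one, which differs from the quantity in the power statement. Baseline 2 samples may also be missing, and a complete-case model would then lose randomised participants. Both are real but manageable.

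**An SAP may fill this in.** A covariate list left to the SAP would be no finding. Here, though, the article states a rule. An SAP that named the strata or Baseline 2 status as fixed covariates would contradict that rule, and the two texts would need aligning.

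**Conclusion.** The point holds for the abstinence model. As written, the rule excludes the three stratification factors by construction, usually excludes Baseline 2 smoking status, and leaves the covariate set open until outcome data are seen. In the PHQ-9 model it excludes only patch use and site.

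The cost is efficiency: about 0.5 to 2 points of power for the strata alone, and about 2 to 22 points against the rule once Baseline 2 status is added. The range depends on an assumed odds ratio of 3 to 10, an assumed within-subject correlation of about 0.1 to 0.5, 50% abstinence at Baseline 2, and the p < 0.10 reading of imbalance. The top of the range needs both a very strong predictor and a low correlation, so it should not be quoted alone.

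A reader might also infer from step 1 that the trial is badly underpowered. That is a separate question and is not settled here, because a different parameterisation of the longitudinal odds ratio cannot be ruled out.

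**What to change.** - Delete the imbalance-and-p < 0.10 rule from both primary models.
- Abstinence model: prespecify the three stratification factors and Baseline 2 smoking status as fixed covariates.
- PHQ-9 model: keep baseline PHQ-9 and add patch use and site.
- State how a missing Baseline 2 sample is handled so that every randomised participant stays in the analysis, for example by using self-report or a missing-indicator category.
- Report a standardised (marginal) risk difference beside the adjusted odds ratio, and say that the latter is conditional.

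The two named follow-up covariates, cardiac rehabilitation attendance and outside treatment, are not addressed by this point.

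The cost is analysis wording, settled before unblinded outcome data are examined. No new data collection is needed.
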